### Pilot study

Prior to the study, the survey instruments will be piloted in one school that will not be included in the study by the researcher/fieldworkers. It will be important to test the questionnaire and measurement instruments to eliminate any ambiguity in the questions asked in the questionnaire and to correct any difficulties experienced before the main study. The pilot study will follow the same procedures as the main study but use different schools. The data from the pilot study will not be included in the main study. Confidentiality of the participants will be maintained at all times throughout the pilot and main study. The participant’s name or any personal details relating to the participants will not be mentioned in any publication, report or meetings where results of the researcher are being presented.

### Data collection instruments and techniques

Table 1 below identifies and describes the measures to be assessed and techniques utilized in the i-SPAN study.

**Table 1 Tab1:** Measures to be assessed and techniques utilized in the i-SPAN study

Measures assessed	Target audience	Phase of study	Instrument or standard practice utilized and its description
Focus group discussions (FGDs)	a. Selected school governing body members b. Selected learners in grades four and seven	Phase 1- Elicitation phase	An interview schedule has been developed by the research team and will be used as a guide during the FGDs to explore current practices at each school. All FGDs will be audio-recorded and conducted in the language of choice by fieldworkers. The audio-recordings will be sent to an external transcriber who will transcribe verbatim.
Structured in-depth interviews (IDIs)	School principals	Phase 1- Elicitation phase	An interview schedule has been developed by the research team and will be used as a guide during the IDI regarding health promotion in schools.
Questionnaire	a. LO educator b. Learners c. Parents of learners	Phase 2- Intervention phase	The questionnaires will be designed and adapted from questionnaires used in previous school intervention studies [23–25]. a. Educators will complete a pre and post intervention questionnaire based on diet and physical activity. b. Demographic data, diet and physical activity questionnaires for children and adolescents will be collected. Questionnaires will include pictures for food choices to enhance the learning activities. c. Same as b. Questionnaires will be sent home with the participating learners and asked to be returned within the same school week Reliability of the questionnaire will be ensured as follows: During the training of the fieldworkers’ changes/amendments to the questions will be made to ensure that there is clarity and no ambiguity in the questions being asked of all participants. The questionnaires will be translated into isiZulu by a person familiar with the content and back-translated into English by an independent translator. The questionnaire will be conducted in the language of choice (English or isiZulu) of the participant. The activities during the intervention will be conducted in English but as the children are young, the fieldworkers will be able to assist them in isiZulu whenever needed. Questions will further be refined during and after the pilot study to further detect any ambiguity or difficulty.
Anthropometry	Weight and height for all participating children and adolescents	Phase 2- Intervention phase	Weight and height will be measured using a digital weighing scale, and stadiometers. (Model no. 210/217/876; Seca, Hamburg, Germany). The weight of the participant will be taken to the nearest 0.1 kg for accuracy. The participants will be weighed with minimal clothing, and preferably with an empty bladder and before a meal [26]. Measurements using the stadiometer will be taken to the nearest 0.1 cm for accuracy. The participants will be measured without shoes. Participants are required to stand with their legs straight, heels and the height measure touching at the back, arms at the sides, relaxed shoulders, with chin level to ground and looking straight ahead [26]. Weight and height measurements will be taken in duplicate for accuracy and a correct average. The body mass index (BMI) for age Z scores, according to the 2006 WHO Growth Standards for children, will be used to classify being at risk of overweight with a Z score of SD 1, overweight with a Z score SD > 1 and obese as a Z score SD > 2 [27].
Workshop	LO educators	Phase 2- Intervention phase	To facilitate study implementation, educators will be invited to attend a two-day training workshop at the university to assist educators in understanding and delivering the classroom lessons as part of the intervention. They will also be provided with the findings of the baseline data to assist them.
Health Promotion Toolkit	Schools randomized into intervention arm	Phase 2- Intervention phase	The toolkit consists of the learner pamphlet, the educator manual, and sports box. a. The pamphlet includes all relevant information for learners and simplified regarding overweight and obesity. b. Instead of being a stand-alone school subject, physical education became one of the four learning outcomes of the LO subject of the new curriculum, thus not receiving adequate attention as an important part of healthy living for the learner outcomes [28]. The educator manual has been developed and adapted from teaching manuals in previous nutrition and school-based intervention studies [29, 30]. The manual consists of collated materials that constitutes the learner outcomes of the Life Orientation curriculum. The LO learner outcomes, as per the South African National Curriculum, include health promotion, as well as social, personal and physical development and movement [28]. The manual explains the significance of the obesity epidemic in South Africa and in children, the purpose of the manual, the goals and objectives of the i-SPAN study, as well as the monitoring and evaluation processes. The intervention and lesson plans are designed so that educators have some level of flexibility as topics may overlap. Activities are also included after every lesson to assist educators and make the lessons more enjoyable for the learners. If lessons similar to those in the manual are being conducted, then the manual will serve as a reinforcing tool for the educators. However, if the nutrition and physical activity components are not part of a school LO classroom lesson plan, then the educators will be introduced to and assisted with understanding the importance of the healthy lifestyle components during the educator workshops that will take place prior to commencement of the study. c. The Department of Sport and Recreation South Africa actively promotes the options of indigenous games as recreational or formal games. There are ten games have been identified as part of an indigenous games national project. These include: dibeke (a running ball game); diketo (a coordination game); kgati (a rope jumping game); ncuva (a board game); morabaraba (a board game); jukskei (a throwing and target game); kho-kho (a running game); Iintonga (a stick fighting game); arigogo (similar to rounders) and drie stokkies (running and jumping game). It is important to capitalize on such opportunities as they serve as inexpensive, culturally and context-specific tools that contribute to child health. Therefore, members from the Department of Sports and Recreation will assist the educators and fieldworkers during the physical activity times (this will be negotiated with LO teachers and principals for suitable times such as during breaks, after school and during the specific physical activity times as indicated by stakeholders within the four sub-districts). It will not be possible to include all games but the Department of Sports and Recreation has proposed teaching the learners at least a few of the indigenous games that they are familiar with, their parents know of or basically introducing it as a novel experience to them.

All instruments and measurements will be conducted for each school in a scheduled visit, unless alternate arrangements are made to revisit the school for data collection. The control schools will not receive the health promotion toolkit but will follow the regular LO syllabus

### Behavioural outcomes

We believe there are two important behaviour change outcomes that can be achieved from the study, i.e. healthy food choices and increased food variations, and increased physical activity participation during school hours. Table 2 below describes the two behavioural outcomes and the anticipated change based on the SCT model [22].

**Table 2 Tab2:** Social cognitive theory constructs embedded in the interventions

Use of Social Cognitive Theory grounded in the interventions			
SCT constructs	Cognitive component	Behaviour component	Environment component
Knowledge of health benefits and risks [22, 31, 32]	Assess the health promotion status in the iLembe district schools and identify the extent to which health promotion has been utilized in the schools (regarding diet and physical activity) by interviewing principals and conducting an interview with principals at baseline. Nutrition education based on current knowledge- questionnaires that identifies health benefits and risks will be conducted at baseline and post-intervention to assess if there is a significant change in knowledge based on the interventions.	Healthy eating activities; physical activities Food evaluation: classroom lessons will be designed to assist learners on the risks associated with unhealthy eating, sedentary behaviours, and encourage the learners to bring healthy snacks to school. As the children and adolescents may receive either breakfast or lunch from the school feeding scheme, they can evaluate their meals accordingly.	Food policy to be reviewed or implemented; less energy-dense foods and sugar-sweetened drinks to be sold in school tuck shops and by vendors.
Perceived self-efficacy [22, 33]	Promote positive body image through classroom lessons, hand puppets; children can become empowered to make correct decisions regarding their health. Through having the knowledge of healthy eating options, unhealthy foods and health risks, as well as sedentary behaviour linked to health conditions, children become more aware of choice and the intention to making correct choices and changing behaviours/attitudes that benefit them e.g. less intake of sweetened juices, energy-dense snacks when given the options	Find differences between foods that are nutrient dense and foods that are low in nutrients and energy- dense- use colouring in competitions to colour in healthy options, role-play of good and bad eating and lifestyle habits, sporting activities that include netball and soccer tournaments and prize-giving.	Interactive homework to work with parents, Barriers to change questionnaire
Outcome expectations [22, 33]	Classroom lessons that focus on fruit and vegetable intake, the Food Pyramid, and how to achieve a balance through healthy eating & physical activity	Taste-testing activities, preparing simple fruit and vegetable snacks, aerobics activities, Self-evaluation of current fruit and vegetable intake	Motivational group discussions will also be conducted with both learners and educators Educators serve as school champions and role models Observing parents cooking at home. Use local media to create health awareness regarding healthy eating and activities
Perceived facilitators [22, 34]	Nutrition education based on current knowledge and experiences, discuss ways to achieve balance through healthy eating & physical activity	Provide opportunities for learners to choose healthier food and snack alternatives (taste-testing)	Exposing learners to healthier foods, participation in learning activities with peer groups, parents and learners to create after school supper menus modified to be lower in fat & higher in fruits and vegetables, choosing water or juice offered instead of cool drink, taking into consideration the costs. Work with vendors to identify unhealthy foods and drinks and replace them with fruits, healthy snacks, encourage learners to drink more clean water

### Mediating and moderating variables

The i-SPAN learner questionnaire will be used to assess any potential mediators, as part of the process evaluation, to identify any possible processes that may mediate diet and physical activity changes. The questionnaire consists of different sections that are able to assess knowledge, attitudes and beliefs, as well as the mediating behaviours of the child and parent that may affect diet and physical activity levels. Possible moderating variables such as sex, weight status and healthy lifestyle behaviours will be obtained from the baseline data of the study. The questionnaires will be administered during the classroom LO lessons by the fieldworkers to ensure that the learners understand the questions.

### Process evaluation

This phase will seek to identify the acceptability and impact of the interventions on the learners, educators and parents. It will also explore the extent to which the health promotion toolkit will be utilised in the intervention schools. Various factors such as facilitating and constraining factors to implement toolkit at the schools, the implementation process, times and durations of implementation will be taken into account. Therefore, to conduct the process evaluation a mixed methods approach will be utilised.

### Planned data collection

The data will be de-identified and available for secondary analyses for student projects. Electronic data quality will be ensured by checking completeness of required variables throughout the data collection process, and will comprise: number of participants correspond to number of questionnaires completed. Absenteeism will be recorded. For data analysis and results, all personal identifiers of participants will be removed during reporting phases. All data will be handled and coded only by the principal investigator and co-investigators who will serve as a data monitoring committee for the study. The principal investigator will also be responsible for auditing trial conduct, as well as any adverse events during the trial. Reports will be presented and made available to the various stakeholders mentioned previously and UKZN to assist in managing and preventing overweight and obesity in childhood. The data will also serve to assist the community i.e. iLembe district in managing and preventing overweight and obesity in children and adolescents. Findings of the study will also be disseminated through conferences and peer-reviewed publications. During the survey if learners are identified as overweight or obese, will be referred for appropriate care to local health facilities as per Department of Health levels of care.

### Planned statistical analysis

#### Descriptive and analytical statistics

The use of weight and height, BMI calculations, completed questionnaires, arising from the interventions will use both descriptive and inferential statistics to analyse the data. To ensure succession of cluster randomization, the presence of any significant differences between the control and intervention cluster for the baseline characteristics of the participants such as sex, age, etc., will be examined using bivariate mixed effect regressions to account sufficiently for the clustered design. Data will be processed and analysed using Stata 13.0 SE. Mixed effects using generalized linear and logistic modelling approaches will be used to compare continuous and binary endpoints respectively among students in schools in intervention and control arms of the study. A within school random effect will be incorporated to account for correlated (repeated) measurements within each school to correctly estimate the significance when comparing pre- and post-intervention periods. Outcome variables include change in BMI at baseline and end of study, dietary intake, time spent in sedentary behaviours, diet and physical activity self-perception and practices, including overall knowledge and attitude regarding diet and physical activity- significant levels and stratified analyses.

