### Participants and recruitment process

The participants of the study will include children in grade four (aged 9-11 years) and grade seven (aged 12-15 years), as well as parents/primary caregivers, Life Orientation (LO) educators, principals, members of the community, the latter through the school governing body (SGB). When the data has been collected meetings will be held with the SGBs (from whom permission will be required prior to the study) to inform them of the results and get their input on the way forward. They will also be the link with the wider community. Other stakeholders will include DoBE, DoH, Sports and Recreation, Health Promotion Coordinators, the District Nutrition Coordinator and School Health Teams in iLembe district, KwaZulu-Natal. The study setting will be primary schools in iLembe district.

A complete list of all schools with grade four and seven children in iLembe district will be provided by the Provincial Department of Basic Education. The list includes over 400 primary schools from which 16 schools will be selected randomly with probability proportional to size (PPS). There will be four schools from each of the four sub-districts, which will be randomly assigned into the two study arms (control *n* = 8, intervention n = 8). Two schools will receive the intervention and two schools will serve as controls in each of the four sub-districts. All children and adolescents in grade four and seven attending these schools and their parents/primary caregiver will be invited to participate in the study. Children and adolescents must provide assent in writing via the consent forms. Parents/caregiver must also provide consent for participation in the study for the children/adolescents and themselves (Additional file 2). South African schools are arranged into quintiles determined by the National Treasury, based on scores reflective of the poverty levels where a community is situated. The DoBE uses these poverty classifications that range from quintiles 1–5, where quintile five is the least poverty-stricken and one is the most poverty-challenged quintile, to classify schools. Most of the primary schools in iLembe district are from quintiles 1 and 2, hence it is important to understand the daily challenges these communities face regarding housing, socio-economic status, employment, as well as health outcomes as these are regarded as schools with low socio-economic status and exempt from school fees [18].

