### Sample size/power calculation

The school is the unit of the study. The power/sample size calculation was performed using a test for two means in a cluster randomized design function implemented in PASS 12 [19]. A power calculation indicated that with 8 schools in each arm and 68 participants per cluster, the study would have 90% power (1-β) to detect an underlying medium standardized difference between the means (effect size) of 0.3 following the intervention, at a two-sided 5% significance level (α), assuming an intra-class correlation coefficient (ICC) of 0.05 or 5% [20, 21].

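### With 16 schools, a school random effect alone does not secure the 5% level: if the arm effect is tested with z and no small-sample correction, type I error is about 7–9% at the protocol's ICC

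*Protocol article*

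**What the plan says.** The sample size section makes the school the unit and plans "with 8 schools in each arm and 68 participants per cluster", tested "at a two-sided 5% significance level (α"), "assuming an intra-class correlation coefficient (ICC) of 0.05 or 5"%. The recruitment section adds that "Two schools will receive the intervention and two schools will serve as controls in each of the four sub-districts".

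The section on descriptive and analytical statistics then states: "Mixed effects using generalized linear and logistic modelling approaches will be used to compare continuous and binary endpoints respectively". It adds a random effect for school, whose declared purpose is that significance be estimated correctly. On software it says only: "Data will be processed and analysed using Stata 13.0 SE". It does not state the estimator (ML or REML), the reference distribution (z, t or F), the degrees of freedom or any small-sample correction.

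**The concern.** A school random effect allows for the existence of between-school variance. It does not allow for the fact that this variance is estimated from only 16 schools. A z test treats the estimate as if it were the true value, and maximum likelihood also makes the estimate too small on average. Measuring more learners per school does not help, because the arm contrast is a contrast of school means.

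The analysis section therefore credits the random effect with more than it can deliver at this number of clusters. If nothing further is done, the level in the sample size section is not the level of the analysis, and 95% intervals are too narrow. The same model family is planned for the BMI outcome and for the diet, activity, knowledge and attitude outcomes, so the problem would recur in each. The Discussion says that a positive result would lead to use in the control schools and in further schools, so a false positive would have consequences.

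**Working it through.** **Inputs.** All are from the protocol article: 8 schools per arm, 68 participants per school, ICC 0.05, two-sided 5%, standardized difference 0.3 (sample size section), and two schools per arm in each of four sub-districts (recruitment section). Assumed here, because the document gives no figure: equal cluster sizes, and for the binary outcome a prevalence of about 20% with the ICC on the latent logistic scale.

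**The plan's own figures.** The 5% is a design level; the document gives no achieved type I error to reproduce. It does state that "the study would have 90% power (1-β"), and this does not reproduce:
- Design effect = 1 + (68 − 1) × 0.05 = 4.35.
- Effective n per arm = 8 × 68 / 4.35 = 544 / 4.35 = 125.1.
- SE = √(2 / 125.1) = 0.1265, and 0.3 / 0.1265 = 2.372.
- Normal power = Φ(2.372 − 1.960) = 66.0%. Noncentral t on 14 df gives 59.8%.

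The gap from 90% is a separate matter. The two power figures serve here only to price the remedy.

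**Degrees of freedom.** 16 schools − 2 arm means = 14. Fitting four sub-districts uses 3 more, leaving 11.

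**Closed form, arm only, z critical value 1.960.**
- REML: the between-school sum of squares is divided by 14, so the ratio follows t on 14 df. Type I error = 2 × P(t14 > 1.960) = 7.02%.
- ML: the same sum is divided by 16, so the SE shrinks by √(14/16) = 0.935 and the effective cut-off is 1.960 × 0.935 = 1.833. Type I error = 2 × P(t14 > 1.833) = 8.81%.

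**Simulation.** Balanced random-intercept linear model, arm only, 400,000 null trials per row, negative variance estimates set to zero:

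| ICC | REML, z | ML, z | REML, t on 14 df |
|---|---|---|---|
| 0.005 | 5.6% | 6.6% | 3.8% |
| 0.01 | 6.4% | 7.7% | 4.4% |
| 0.02 | 6.9% | 8.6% | 4.9% |
| 0.05 | 7.0% | 8.7% | 5.0% |
| 0.10 | 7.1% | 8.9% | 5.1% |

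The ICC 0.05 row agrees with the closed form. Every z entry is above 5%. At ICC 0.05, ML with t on 14 df still gives 6.4%, so the estimator matters as well as the reference distribution. With sub-district terms, REML with z gives 7.6% and REML with t on 11 df gives 5.0%.

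**Logistic model.** Random intercept, Wald z, 1,500 null trials per setting: 8.7% at ICC 0.05 (Monte Carlo SE 0.7 points) and 6.6% at ICC 0.02 (SE 0.6 points).

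**Interval width after correction.**
- From REML and z: 2.145 / 1.960 = 1.09 (14 df); 2.201 / 1.960 = 1.12 (11 df).
- From ML and z, 14 df: 1.094 × √(16/14) = 1.17.

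**The case against.** The strongest objection is that the protocol never commits to a z test. Its wording fits REML with t on 14 degrees of freedom, which holds 5.0% at ICC 0.05, just as well as it fits ML with z. Estimator and degrees of freedom are often left to an analysis plan, and none is shown here. This stands to the extent that the error rates must be stated conditionally. It does not remove the point, because the section goes beyond silence: it presents the school random effect as what makes the significance correct, and with 16 schools that is not enough.

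Three stronger readings are tempting, and the documents do not support them.
- A reader might infer from the software named that the analysis will run at 7–9%. The document names no command or test option, and a package's usual output is not the plan's chosen test.
- A reader might quote about 13%. That figure needs ML, z and fixed sub-district terms together (2 × P(t11 > 1.960 × √(11/16)) = 13.2%). The analysis section plans no sub-district terms.
- A reader might apply 7–9% to every outcome. The ICC of 0.05 is a planning value for a comparison of means. No ICC is given for change in BMI or for the other outcomes, and at very small ICCs the excess with REML is under one point.

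**Conclusion.** The point holds in conditional form. With 16 schools and ICC 0.05, a z test of the arm effect without small-sample correction has a type I error of about 7.0% (REML) or 8.7–8.8% (ML) in the linear model, and about 8.7% in the logistic model. Nominal 95% intervals from the linear model would then cover about 93% (100 − 7.0) or 91% (100 − 8.8). Over ICC 0.005 to 0.10 the linear range is 5.6–7.1% (REML) and 6.6–8.9% (ML).

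This rests on equal school sizes, normal school effects, an arm-only model and, for the binary outcome, the assumed prevalence. If the sponsor already intends a t reference on between-school degrees of freedom, only the statement is missing.

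**What to change.** Add one sentence to the analysis section, fixed before any outcome data are compared by arm. Continuous outcomes are fitted by REML and the arm effect is referred to a t distribution on between-school degrees of freedom: 14, or 11 if sub-district is fitted. Where the software offers no such degrees of freedom, use a t-test on the 16 baseline-adjusted school means. For overweight and obesity, keep the logistic model and its effect measure, and refer the arm effect to t on the same between-school degrees of freedom.

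Costs:
- Intervals are about 9–12% wider than with REML and z, and about 17% wider than with ML and z at 14 degrees of freedom.
- Power at the stated inputs is about 60% rather than 66%.
- If the true ICC is very small the t test is conservative (3.8% at ICC 0.005).
- The t reference was not simulated for the logistic model. Since ML with t stays at 6.4% in the linear model, some excess may remain there.

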**Methods:**

We will employ a mixed method study design which is divided into two phases. Phase 1, namely the qualitative elicitation research phase will inform the development of the quantitative intervention phase (phase 2), consisting of a cluster-randomized trial, based on input from key stakeholders. The study will be undertaken in 16 government-funded primary schools in the iLembe district of KwaZulu-Natal, South Africa. The study will target learners in Grades 4 and 7, their parents, Life Orientation educators, school principals and members of school governing bodies. Assessment for the primary objective (BMI Z scores), and the secondary objectives (change in knowledge, attitudes and behaviours regarding diet and physical activity) in both study arms will be conducted at baseline in March 2020 and at the end of the study in October 2020.

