### Study components and implementation

The study will consist of two phases: Phase 1 is a baseline elicitation phase using a qualitative paradigm, whereby the formative assessment will inform the development of the intervention for use in phase 2. A thorough search and review of available scientific literature will be carried out to determine what is currently being done regarding learners, particularly in respect to health promotion concerning physical activity and dietary habits of school-going learners in South Africa and specifically in iLembe district, KwaZulu-Natal. During the elicitation phase focus group discussions (FGDs) will be conducted with selected members of the SGB, as well as selected children and adolescents in grades four and seven to explore current practices at each school. In-depth interviews will be conducted with principals regarding nutrition and PA at school. Based on the information obtained from the elicitation research phase, a plan for the intervention phase based on the Social Cognitive Theory (SCT) framework [22] will be developed and implemented. During the intervention phase structured questionnaires will be given to the children and adolescents in grades four and seven, the LO educators and the parents/primary caregivers of the participating children and adolescents to determine their understanding, knowledge, attitudes and behaviours regarding diet and physical activity at baseline and at the end of the study.

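### The pre/post analysis does not say whether each child contributes one record or two; with two records and the school effect as the named random effect, the standard error is not valid

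*Protocol article*

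**What the plan says.** Under Descriptive and analytical statistics, the protocol article gives the model family: "Mixed effects using generalized linear and logistic modelling approaches will be used to compare continuous and binary endpoints respectively". It continues: "A within school random effect will be incorporated to account for correlated (repeated) measurements within each school to correctly estimate the significance". The use to which this is put is given as "when comparing pre- and post-intervention periods". No other random effect or residual correlation is named. The next sentence opens the list of outcomes: "Outcome variables include change in BMI at baseline and end of study", followed by dietary intake, sedentary time, practices, knowledge and attitude.

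The abstract places assessment "in both study arms will be conducted at baseline in March 2020 and at the end of the study in October 2020". Study components and implementation has the children questioned on "knowledge, attitudes and behaviours regarding diet and physical activity at baseline and at the end of the study". Both time points fall in one school year and all grade four and seven learners of the chosen schools are invited, so the same children are measured twice. The objectives for phase two are BMI Z score, the proportion overweight and obese, and knowledge, attitude and behaviours. The abstract describes the last group as change.

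**The concern.** The paragraph gives the school effect the task of handling repeated measurements and says that significance will then be correct. That holds if each child supplies one change score. It does not hold if each child supplies a March record and an October record, for two reasons that pull in opposite directions:

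- Given school, the model treats a child's two values as independent. Positive within-child correlation makes the arm-by-period contrast more precise than the model believes, so the reported standard error is too large.
- A single school effect shared by both periods leaves no room for schools to move differently between March and October. That school-by-period variance is the relevant error for a contrast randomised by school, and omitting it makes the reported standard error too small.

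Nothing makes the two errors cancel. At stake is whether the p-values and confidence intervals for the intervention effect have their nominal properties: a real effect may be missed on one outcome and a chance one declared on another.

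**Working it through.** **Inputs from the protocol article.** Sample size/power calculation: "with 8 schools in each arm and 68 participants per cluster", that is 8 × 68 = 544 children per arm, and ICC 0.05. Two time points.

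**Assumptions, not in the document.** r is the correlation between a child's two values given school. CAC is the share of the school variance common to both periods. Total variance is set to 1, so school variance is 0.05 and child-level variance 0.95.

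**The plan's own figure.** The article gives no standard error for this contrast. Its only figure from these inputs is 90% power, which does not reproduce: the design effect is 1 + 67 × 0.05 = 4.35, the effective size 544/4.35 = 125.1 per arm, and the power for 0.3 SD about 66%. That is a separate matter and does not enter the comparison below.

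**Standard error reported by the two-record, school-intercept model.**
Variance ≈ (2/8) × 2 × [0.95 + 0.05(1 − CAC)]/68. At CAC 1 this is 4 × 0.95/544 = 0.00699, SE 0.0836.

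**True standard error of the arm-by-period contrast.**
Variance = (2/8) × [2 × 0.05(1 − CAC) + 2 × 0.95(1 − r)/68].

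- r 0.9, CAC 1: 0.25 × (0 + 0.00279) = 0.00070, SE 0.026
- r 0.9, CAC 0.5: 0.25 × (0.05 + 0.00279) = 0.01320, SE 0.115
- r 0.5, CAC 0.5: 0.25 × (0.05 + 0.01397) = 0.01599, SE 0.126

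The last column is the type I error in simulations of the null case (16 schools × 68 children × 2 times, REML fit with a school intercept, 250 runs per row, nominal 5%).

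| r | CAC | Model SE | True SE | Model/true | Simulated type I error |
|---|---|---|---|---|---|
| 0.9 | 1 | 0.084 | 0.026 | 3.16 | 0% |
| 0.9 | 0.8 | 0.084 | 0.076 | 1.11 | 2.4% |
| 0.9 | 0.5 | 0.085 | 0.115 | 0.74 | 16.4% |
| 0.5 | 1 | 0.084 | 0.059 | 1.41 | 0% |
| 0.5 | 0.8 | 0.084 | 0.092 | 0.91 | 9.6% |
| 0.5 | 0.5 | 0.085 | 0.126 | 0.67 | 19.2% |

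A school-level analysis of each child's change, on the same simulated data, rejected in 2.4% to 6.8% of runs. That is near nominal: the Monte Carlo standard error at 5% is √(0.05 × 0.95/250) = 1.4 points.

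**Which direction is plausible.** It helps to express the drift as an ICC of change.

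- At r 0.9 the child variance of change is 2 × 0.95 × 0.1 = 0.19. If the ICC of change were 0.05, the school variance would be 0.19 × 0.05/0.95 = 0.01 and the true SE √[0.25 × (0.01 + 0.00279)] = 0.057. The model's 0.084 is then conservative.
- The two agree at r 0.9 when the school variance of change is about 0.0255, an ICC of change of 0.0255/(0.0255 + 0.19) ≈ 0.12. Anti-conservative error needs more than that.
- At r 0.5 the child variance of change is 0.95, and an ICC of change of 0.05 is the CAC 0.5 row (0.05/(0.05 + 0.95)), with type I error of about 19%.

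So the same ICC of change gives a conservative test on a highly stable outcome and an anti-conservative one on a less stable outcome. These figures are for continuous outcomes. The structural argument carries over to the logistic model, but no size was computed for it.

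**The case against.** The strongest reply is that the article already frames its outcomes as change: BMI in the analysis section, and the knowledge, attitude and behaviour outcomes in the abstract. One change score per child with a school random intercept is valid. This stands, and it removes the problem wherever that model is meant. It does not cover the overweight/obese proportion, which goes to a logistic model with no change form stated. Nor does it explain why the school effect is said to handle repeated measurements over two periods.

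A second reply is that the article does not call the school effect the sole random effect, that the odd phrase about an effect within school could mean children nested in schools, and that a condensed article may leave the covariance structure to a fuller plan. This also stands in part. A reader might infer that the plan rules out a child-level term, but the text does not say so. What can be criticised is the statement that the named effect is enough to make significance correct, which is true of one form of the model and not of the other.

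A reader might also infer that the primary BMI Z comparison carries an inflated false-positive rate. The documents do not support that. They give neither r nor CAC; if BMI Z is highly correlated within child, as is likely over seven months, inflation needs an ICC of change above about 0.12, more than twice the 0.05 that the article assumes for its outcome. Intermediate settings show little distortion (ratio 1.11 at r 0.9, CAC 0.8).

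**Conclusion.** The concern holds in a conditional form. The paragraph mixes two models, and its assurance of correct significance is justified for only one of them. If two records per child are fitted with the school effect as the named random effect, the reported standard error of about 0.084 SD may be up to 3.2 times too large (r 0.9, no school-specific drift; power lost) or about two thirds of the true value (r 0.5, CAC 0.5; type I error about 19%). For BMI Z the likely error is conservative. Anti-conservative error is a risk for less stable outcomes if those are fitted as two records. The overweight/obese outcome is where the gap is clearest. The size rests on assumed r and CAC, equal school sizes of 68 and ICC 0.05. Drift common to all schools does no harm, since a period term absorbs it. This should be fixed before the data are analysed, but it is not a fatal flaw in the design.

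**What to change.** State that each child contributes one record: the October value compared between arms, adjusted for that child's March value, with a school random intercept. Use a linear model for BMI Z and other continuous outcomes and a logistic model for overweight/obese. With 16 schools, apply a small-sample degrees-of-freedom correction where the software offers one. This keeps the random effect that the article already names, is valid whichever reading was intended, and generally gains precision over a plain change score.

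If both time points are to stay in one model, nest child within school, add a school-by-period random effect, and name the arm-by-period interaction as the intervention effect.

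The cost is a change of analysis wording. Both measurements are already planned, and no new data are needed.
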